**Table 10: Precision estimates for proportions of subjects with new drug resistance mutations detected**

| Sample size | 10 | 20 | 30 | 40 | 50 | 100 |
| --- | --- | --- | --- | --- | --- | --- |
| 95% confidence interval (+/-) | .31 | .23 | .19 | .16 | .14 | .10 |

With the increased study size compared to the pilot project, we will perform a definitive analysis to assess the impact of low-frequency mutations on time to virologic suppression (defined as HIV-1 RNA less than 50 copies/mL). Survival analyses will evaluate the time to virologic suppression among subjects with transmitted low-frequency HIV-1 drug resistance mutations detected who are on ARV regimens with fewer than three active agents compared to subjects without transmitted HIV-1 drug resistance, controlling for the baseline HIV-1 RNA level. If a significant difference is detected, we will use additional Cox proportional hazard models to explore characteristics (e.g. HLA type, specific mutation or class of ARV therapy, and timing of ARV treatment) that might impact time to virologic suppression.

We will also perform a survival analysis evaluating the time to virologic failure among subjects with transmitted low-frequency HIV-1 drug resistance mutations who are on ARV regimens with fewer than three active ARV agents compared to subjects without transmitted HIV-1 drug resistance, controlling for baseline HIV-1 RNA level and the timing of initiation of ARV therapy. For purposes of this analysis, virologic failure will be defined as any one of the following:

1) Failure to suppress viral replication (HIV-1 RNA greater than 400 copies/mL after 24 weeks or greater than 50 copies/mL on two occasions after 48 weeks)

2) Addition or substitution of ARVs because of delay in viral suppression

3) Detectable HIV-1 RNA (greater than 400 copies/mL) on two consecutive occasions following viral suppression

In the pilot study, only *four subjects were* observed to have virologic failure during follow-up. It is likely that, even with a larger sample size and longer follow-up, we will have limited power to detect associations between the time to virologic failure with either transmitted HIV-1 drug resistance or the timing of ARV therapy. Time to virologic suppression has been evaluated by other studies [52, 53, 56, 190], and this outcome and other markers of early treatment response have been associated with longer-term treatment outcomes [191-193]. This issue will be discussed further under **D.6 Limitations, alternatives, and approaches to anticipated problems.**

If significant numbers of any one specific mutation (e.g. M184V) are identified, we will explore the impact of that mutation on the virologic outcomes described above. Further evaluations of the clinical impact of low-frequency HIV-1 drug resistance mutations will also be performed.

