At the recommendation of reviewers, we have deferred this resubmission until our pilot project was completed; the findings are not significantly different from what we previously described. The overall prevalence of transmitted HIV-1 drug resistance is somewhat lower (34% versus 46%) because subjects were studied in reverse chronologic order, and those recently studied were among those enrolled prior to 2000. However, we remain confident that the primary objectives of each of the aims will be sufficiently powered with continued enrollment of subjects with acute HIV-1 infection and their putative source partners during a planned five-year study period, as described in detail in **5. Research Design and Methods.**

Other concerns of reviewers are addressed below. Changes to the submission are indicated by italicized text.

Critique #1:

1. "…the proposed research … would not likely affect treatment options of HIV infected individuals." and "Most importantly, is this study relevant to clinical significance as patients can be diagnosed to be in virological failure and function normally with the diagnosis of acute HIV infection."

As mentioned above, results from these studies could modify current treatment practices. We agree with Reviewer #1 that low-frequency mutations may not, in fact, uniformly reduce the efficacy of ARV therapy, and there may be negative consequences if clinicians unnecessarily avoid effective ARV agents in favor of more complicated regimens. It also should be determined, even if low-level mutations are clinically relevant, if use of more-sensitive HIV-1 drug resistance assays prior to initiation of ARVs would be cost-effective.

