*Eighty-three (88%) of the 94 subjects initiated ARV therapy a median of 45 (IQR 24-107) days after HIV-1 infection. Four (5%) subjects who initiated ARV therapy had HIV-1 drug resistance mutations identified by consensus sequencing, 24 (29%) subjects had low-frequency mutations identified only by OLA, and 55 (66%) subjects had no mutations that were detected by either assay. At the start of ARV therapy, the mean CD4+ T-cell count was 451 (SD 197) cells/mm3 in subjects with low-frequency mutations and 479 (SD 168) cells/mm3 in subjects with no detectable mutations (p=.5). The mean HIV-1 RNA level at the start of treatment was 5.0 (SD 0.8) log10 copies/mL in subjects with low-frequency mutations and 4.8 (SD 1.0)* *log10 copies/mL in subjects with no detectable mutations (p=.4).*

*Survival analyses evaluated the time to virologic suppression (HIV-1 RNA less than 50 copies/mL) among treated PIC subjects. The HIV-1 drug resistance mutations that were detected in either plasma or PBMCs from each subject were evaluated with the Stanford University HIV Drug Resistance Database [151] in order to estimate the number of active agents in a subject's treatment regimen. An ARV agent was considered to be inactive if the mutation conferred high or intermediate-level resistance to that ARV. Cox proportional hazard models compared subjects with low-frequency HIV-1 drug resistance mutations receiving fewer than three active ARV agents ("inadequate" regimens) to subjects with low-frequency HIV-1 drug resistance mutations receiving at least three active ARV agents and to subjects without detectable mutations. Analyses were adjusted for HIV-1 RNA level at the time of initiation of ARV therapy.* ***Figure 4*** *shows the Kaplan-Meier curve indicating time to virologic suppression. After adjustment for the HIV-1 RNA level at the start of ARV therapy, the hazard ratio for time to virologic suppression was 1.1 (95% CI 0.54-2.3, p=.8) for 14 subjects with low-frequency HIV-1 drug resistance mutations who received fewer than three active ARV agents and 2.3 (95% CI 1.1-4.6, p=.02) for ten subjects with low-frequency mutations treated with at least three active agents, compared to 55 subjects without detectable mutations. (Note: a hazard ratio less than 1 indicates a longer time to virologic suppression, and a ratio greater than 1 indicates a shorter time to virologic suppression.).*

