**Aim #2: Quantify the increase in detection of low-frequency mutations in PBMCs during ARV therapy.**

Primary objectives:

1) Compare the proportion of subjects with transmitted HIV-1 drug resistance that have new HIV-1 drug resistance mutations detected in PBMCs 6 and 12 months after the start of ARV therapy compared to subjects without transmitted HIV-1 drug resistance at baseline.

2) Evaluate time to virologic suppression in subjects with transmitted HIV-1 drug resistance compared to subjects without transmitted HIV-1 drug resistance.

Secondary objectives:

1) Explore whether the timing of ARV therapy impacts the increased detection of low-frequency mutations, time to virologic suppression, or time to virologic failure.

2) Explore whether specific mutations (e.g. M184V) are selected for by ARV therapy and are found at a greater level over time within treated subjects with and without HIV-1 drug resistance at baseline.

3) Explore whether specific HIV-1 drug resistance mutations are associated with significant differences in time to virologic suppression and time to virologic failure compared to subjects without transmitted HIV-1 drug resistance.

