| Percent of subjects with no mutations at baseline who have new mutations detected after start of ARVs | 10% | *316/158* | *102/51* | *54/27* | *35/18* |
| 20% | *-* | *461/231* | *133/67* | *66/33* |
| 30% | *-* | *-* | *559/280* | *153/77* |
| 40% | *-* | *-* | *-* | *609/305* |

alpha = 0.05, power = 80%

The sample size for this aim will be motivated by a two-sample test of proportions that will compare the percentages of subjects with low-frequency mutations at baseline who have new mutations detected during ARV therapy compared to the percentage in subjects who had no mutations detected at baseline (**Table 9**). Estimates for the sample size calculations were informed by two small studies that identified increased numbers of HIV-1 drug resistance mutations in two (22%) of nine [32] and six (40%) of 15 [33] ARV-naïve subjects during ARV therapy. Based on these calculations and assuming that one-third of subjects will have transmitted drug resistance, a sample size of *53* treated subjects (*18 subjects with and 35 without drug resistance detected at baseline*) will have 80% power to detect a significant difference in the two groups if 50% of the subjects with baseline mutations and 10% of the subjects without baseline mutations have additional HIV-1 drug resistance mutations detected in PBMCs after the start of ARV therapy. There were 20 subjects who were studied as part of the pilot project who enrolled in the PIC Cohort study within 30 days of HIV infection, received ARV therapy for at least six months, and achieved virologic suppression. Another *twenty* subjects have enrolled in the PIC Cohort since the pilot study began and have received treatment *for at least six months*. If we estimate that *33*% of newly-enrolled subjects will initiate ARV therapy *in the first year of* follow-up *and assume a 10% loss-to-follow-up rate in the first year*, we would need to enroll *42* subjects in addition to these *40* subjects in order to achieve the desired sample size of *53* treated subjects (***Figure 5***)*.*

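### The time-to-suppression analysis in Aim 2 is called definitive because of increased study size, but it has no stated analysis set, sample size or power, and its contrast is not the one in primary objective 2

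*Protocol*

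**What the plan says.** Section 5.b, Aim #2, primary objective 2 reads: "Evaluate time to virologic suppression in subjects with transmitted HIV-1 drug resistance compared to subjects without transmitted HIV-1 drug resistance".

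Section 5.c.2, in the paragraph after Table 10, says: "With the increased study size compared to the pilot project, we will perform a definitive analysis". The comparison described there is between subjects with low-frequency mutations on regimens with fewer than three active agents and subjects without transmitted resistance, controlling for baseline HIV-1 RNA.

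The sample size comes from elsewhere in the same section: "The sample size for this aim will be motivated by a two-sample test of proportions". That test concerns new mutations in PBMCs. It leads to 53 treated subjects, split as "18 subjects with and 35 without drug resistance detected at baseline". Eligibility for the longitudinal study in 5.c.2 requires enrollment within 30 days of infection and HIV-1 RNA below 50 copies/mL within six months of starting ARVs.

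Section 4.g reports the pilot Cox model for the same outcome. There were 14 subjects with low-frequency mutations on fewer than three active agents (HR 1.1, 95% CI 0.54-2.3) and 10 on at least three (HR 2.3, 95% CI 1.1-4.6), each "compared to 55 subjects without detectable mutations". On the covariate, 4.g says: "Analyses were adjusted for HIV-1 RNA level at the time of initiation of ARV therapy".

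Section 1 (response to Critique #1, item 4) states that every primary objective has adequate power at the anticipated sample size.

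**The concern.** The claim of a larger study is the only support offered for calling this analysis definitive, and no stated figure backs it. The analysis carries weight: section 5.f.4 concedes limited power for time to virologic failure and offers time to suppression in its place.

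The stated question and the planned comparison also differ. The comparison leaves out resistant subjects on at least three active agents and those with mutations found by consensus sequencing. A result could therefore be reported against primary objective 2 without addressing it.

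Finally, if the aim's entry criterion is carried over, slow suppressors and non-suppressors are removed before time to suppression is measured. An adverse effect of resistance would show in exactly those subjects.

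**Working it through.** **1. The plan's own figure.** Table 9 gives "alpha = 0.05, power = 80" percent. A two-sided, continuity-corrected two-proportion calculation for 10% versus 50%, with groups in a 2:1 ratio, gives 35 and 17.5, rounded to 18, so 53. All ten filled cells of Table 9 reproduce this way. Accrual: 40 + 42 × 0.33 × 0.9 = 52.5, about 53. The 53 is correct for new mutations; it was never calculated for time to suppression.

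**2. Size against the pilot.**
- Pilot Cox model: 14 + 10 + 55 = 79.
- Stated Aim 2 sample: 53, of which 20 are pilot subjects.
- With all 80 prospective enrollees of section 5.a: 40 + 80 × 0.33 × 0.9 = 63.8, about 64.
- Pooling the whole pilot model with later starters: 79 + 20 + 42 × 0.33 × 0.9 = about 111. Only this exceeds 79. It is not stated for this analysis, and the Aim 2 criteria would not admit all 79.

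**3. Numbers for the planned contrast (assumed splits).** At the pilot share of 14/24, the 18 resistant subjects give 18 × 14/24 = 10.5 on fewer than three active agents. If the 18 include consensus-detected cases at the pilot's 4 in 28, the figure is 18 × 14/28 = 9. So roughly 9 to 11 versus 35, against 14 versus 55 in the pilot. Pooled, about 32 to 33 new starters with a third resistant add 6 to 7 and about 22, giving roughly 21 versus 76.

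**4. Detectable hazard ratio.** With every subject having the event, SE(log HR) = sqrt(1/n1 + 1/n2). The detectable HR at two-sided 0.05 and 80% power is exp(-(1.96 + 0.84) × SE). Power for an assumed HR of 0.5 is Φ(0.693/SE - 1.96).

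The pilot interval gives a check: SE = ln(2.3/0.54)/3.92 = 0.37, whereas the formula gives sqrt(1/14 + 1/55) = 0.30. The scaled columns multiply the SE by 0.370/0.299 = 1.235.

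| Comparison | SE | Detectable HR | Power, HR 0.5 | Scaled HR | Scaled power |
|---|---|---|---|---|---|
| Planned contrast, 9 vs 35 | 0.374 | 0.35 | 46% | 0.27 | 32% |
| Planned contrast, 10.5 vs 35 | 0.352 | 0.37 | 50% | 0.30 | 36% |
| Planned contrast, 11 vs 35 | 0.346 | 0.38 | 52% | 0.30 | 37% |
| Pilot, same contrast, 14 vs 55 | 0.299 | 0.43 | 64% | 0.36 | 47% |
| Pooled, same contrast, 21 vs 76 | 0.247 | 0.50 | 80% | 0.43 | 62% |
| Objective's contrast, 18 vs 35 | 0.290 | 0.44 | 67% | 0.37 | 49% |

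**5. Contrast.** The objective takes any transmitted resistance versus none. The analysis keeps one resistant subgroup, whose pilot HR was 1.1; the omitted low-frequency subgroup had 2.3 (p=.02). Section 4.g notes that values above 1 mean faster suppression.

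**6. Population.** The 5.c.2 eligibility rule makes suppression within six months an entry condition. The same section's definition of virologic failure counts failure to suppress after 24 weeks, which could hardly occur in that population. The survival analyses therefore seem to need a different set, which is not described.

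**The case against.** The 53 belongs to another endpoint and is a floor: its projection counts only ARV starts in the first year, while 5.c.2 admits later starts. The size remark could refer to the whole project (about 100 previous and 80 new subjects, against 100 in the pilot) or to pilot and new subjects combined. This stands in part. A reader might infer that the analysis is fixed at 53 and will hold less information than the pilot; the protocol does not say so. It names no set at all, and every count that follows from its stated criteria (53 to 64) is below 79.

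The HR of 0.5 and the group splits are assumptions, and the Schoenfeld figures are optimistic against the pilot interval. That also stands. A reader might infer that pooling secures 80% power for the planned contrast; the scaled figure is about 62%.

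Baseline RNA is ambiguous, not contradictory. Section 5.a ties baseline to the first available specimen for OLA, but subjects who start ARVs restart at a repeat Entry visit (Table 11 note), so RNA at ARV start may be meant.

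A reader might also infer confounding by calendar period, since section 1 links the lower resistance prevalence to the fact that "those recently studied were among those enrolled prior to 2000" and section 5.e.2 describes changing assay limits. But 5.e.2 also says results censored at 500 copies/mL were re-tested when specimens were available, and nothing shows that era affected suppression.

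Lastly, section 5.f.4 reserves a definitive answer for a later randomized trial, and 5.h.3 acknowledges confounding. That tempers the claim but does not supply its missing basis.

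**Conclusion.** The point holds on two counts. The planned contrast does not match primary objective 2. The claims of increased size and a definitive analysis rest on no stated analysis set, sample size, hazard ratio or power, although section 1 says all primary objectives are adequately powered. A third defect follows if the aim's eligibility rule is applied: the analysis would select on its own outcome.

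For the planned contrast at the only stated treated sample, the detectable HR is about 0.35 to 0.38 with all events, and nearer 0.30 on the pilot's precision. Pooling all starters would bring it to about 0.43 to 0.50, with roughly 62% to 80% power for an HR of 0.5. These figures assume the pilot's 14/24 split, one-third resistant, and an HR of 0.5 that the protocol does not give. The mismatch and the missing basis do not depend on them.

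**What to change.** 1. Define a separate analysis set for time to suppression: all eligible ARV starters with baseline OLA, whether or not they suppress. State whether pilot subjects are pooled. If they are, acknowledge that their results are already known, so the pooled analysis is not an independent confirmation.
2. Make any transmitted resistance versus none the primary contrast, with the pilot's active-agent grouping as secondary. Rewording objective 2 would also remove the mismatch, but would narrow the question.
3. Specify that the RNA covariate is the level at ARV start, as in the pilot.
4. Delete the claims of increased study size and of a definitive analysis, and state the detectable HR for the resulting set and contrast, with the event assumption and a version scaled to the pilot interval.
5. Use calendar period as a sensitivity adjustment only.

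The cost is protocol wording and one recalculation. RNA levels are recorded at regular intervals, and ARV starters repeat the Entry visit, where RNA is measured. The price is a more modest claim and, if pilot data are pooled, reuse of results already seen.

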**5.c.2 Aim #2: Quantify the increase in detection of low-frequency mutations in PBMCs during ARV therapy.**

The primary objectives of the study described in this aim will evaluate changes in the detection of low-frequency mutations in PBMCs over time during ARV therapy and the virologic consequences of ARV therapy in the setting of transmitted low-frequency HIV-1 drug resistance. We hypothesize that, over time, additional mutations will be detected in a greater proportion of treated subjects with transmitted drug resistance compared to treated subjects without HIV-1 drug resistance detected at baseline, because the relative level to which viral replication is suppressed will be diminished in the former group. Secondary analyses will explore associations between specific HIV-1 drug resistance mutations, the interval between HIV-1 acquisition and the start of ARV therapy, the increased detection of HIV-1 drug resistance mutations, and treatment outcomes including time to virologic suppression and time to virologic failure.

This longitudinal study will evaluate subjects enrolled in the PIC cohort within 30 days of the estimated date of HIV-1 infection, who initiate ARV therapy at any point following the baseline evaluation, and who achieve undetectable HIV-1 RNA levels (less than 50 copies/mL) within six months after the start of ARV therapy. OLA will be performed using PBMCs collected at the visit immediately prior to the start of ARV therapy (unless this visit is within 4 weeks from the baseline specimen) and in specimens obtained 6 and 12 months following the start of treatment. The detection of a new mutation will be defined as any mutation detected during follow-up that was never previously detected. Additional analyses will use the semi-quantitative nature of OLA to evaluate the changes in levels of mutations during ARV treatment (i.e. <5%, 5-10%, 10-30%, 30-50% >50% of the viral quasi-species) and the reappearance of mutations that had been detected at baseline but were lost to detection prior to the start of ARV therapy in the absence of ARV selection pressures.

**Table 9: Sample size needed in each arm to detect a difference in proportion of subjects with new low-frequency mutations**

|  | | Percent of subjects with low-frequency mutations at baseline who have new mutations detected after start of ARVs | | | |
| --- | --- | --- | --- | --- | --- |
| 20% | 30% | 40% | 50% |

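### The primary time-to-suppression model controls only for HIV-1 RNA and puts ARV timing behind a significance gate, although the time-to-failure model for the same groups adjusts for timing from the start

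*Protocol*

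**What the plan says.** Protocol, 5.b, Aim #2, primary objective 2: "Evaluate time to virologic suppression in subjects with transmitted HIV-1 drug resistance compared to subjects without transmitted HIV-1 drug resistance".

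Section 5.c.2, in the text after Table 10, gives the analysis. It is presented as conclusive: "we will perform a definitive analysis to assess the impact of low-frequency mutations on time to virologic suppression". Subjects with low-frequency mutations on fewer than three active agents are "compared to subjects without transmitted HIV-1 drug resistance, controlling for the baseline HIV-1 RNA level". No other covariate is named. The next sentence sets the condition for going further: "If a significant difference is detected, we will use additional Cox proportional hazard models to explore characteristics". The listed characteristics include HLA type, mutation or ARV class, "and timing of ARV treatment) that might impact time to virologic suppression".

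The following paragraph makes the same group comparison for time to virologic failure, this time "controlling for baseline HIV-1 RNA level and the timing of initiation of ARV therapy", without any condition.

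Two other places bear on timing. Secondary objective 1 in 5.b reads: "Explore whether the timing of ARV therapy impacts the increased detection of low-frequency mutations, time to virologic suppression, or time to virologic failure". The opening paragraph of 5.c.2 likewise lists the interval from HIV-1 acquisition to ARV start among the factors to be related to suppression in secondary analyses. Neither is conditional on significance. Eligibility in 5.c.2 covers subjects "who initiate ARV therapy at any point following the baseline evaluation".

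**The concern.** Whether to adjust for a covariate should not depend on whether the unadjusted result was significant. Here the gate decides whether the primary comparison is ever seen with timing in the model. The protocol gives timing a possible prognostic role (secondary objective 1). It also raises the possibility that a longer interval weakens the resistance effect (1. Introduction; Aim #2 implications; 3.d). Its own failure model treats timing as a covariate. That outcome had four events in the pilot and the protocol concedes it has limited power, yet it carries the extra term, while the event-rich suppression outcome does not.

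The groups are formed by observation. If timing is prognostic, omitting it pulls the Cox hazard ratio toward 1 and loses power even when the groups are balanced on it. If timing also differs between the groups, the estimate is biased, and the direction depends on facts the protocol does not report.

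**Working it through.** **1. The plan's own figure.** The only Aim 2 power statement is Table 9, which concerns new mutations and not suppression. Inputs: 10% vs 50%, 2:1 allocation (k = 0.5), two-sided 0.05 (sidedness assumed), 80% power.
- Pooled proportion = (0.10 + 0.5 × 0.50)/1.5 = 0.233.
- n = [1.96√(3 × 0.233 × 0.767) + 0.842√(0.09 + 0.50)]²/0.40² ≈ 27.1.
- With continuity correction: (27.1/4)[1 + √(1 + 3/(27.1 × 0.5 × 0.4))]² ≈ 34.2, so 35 and 17.5, rounded to 18. This matches the stated 35/18 = 53.

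No power is stated for time to suppression.

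**2. Size of the planned contrast.** The protocol does not say how many subjects enter the suppression analysis, so 53 is carried over as an assumption. In the pilot (4.g), 14 of 24 treated subjects with low-frequency mutations received fewer than three active agents. Applied to 18, that is 18 × 14/24 = 10.5, so about 11 vs 35.

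**3. Chance that the gate stays shut.** Schoenfeld: power = Φ(√(D·p·q)·|ln HR| − 1.96). If all subjects suppress, D = 45.5, p = 10.5/45.5 = 0.231, and √(D·p·q) = 2.84. Power is 74% at HR 0.4, 50% at 0.5, 31% at 0.6 and 17% at 0.7. A non-significant primary result is therefore quite possible with no confounding at all.

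**4. Effect of omitting timing, balanced groups.** This is a Cox simulation on assumed inputs: 18 vs 35, true resistance HR 0.44, log-hazard 0.5 per SD of RNA, RNA and timing uncorrelated, 1000 replicates.

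| Timing log-hazard per SD | Power, RNA only | Power, RNA + timing | Gain (points) |
|---|---|---|---|
| 0.25 | 68.7% | 70.9% | 2.2 |
| 0.50 | 58.5% | 69.4% | 10.9 |
| 0.75 | 45.6% | 67.4% | 21.8 |

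A separate run gave 72% vs 74%, 59% vs 71% and 50% vs 74%. With about 11 resistant subjects and timing 0.50, it was 45% vs 55%. If RNA is taken at ARV start and correlates with timing, the gain at 0.50 falls from about 13 points at correlation 0 to 9 at −0.5 and 6 at −0.7. At 0.25 it is 1-3 points throughout.

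**5. Imbalanced groups, 11 vs 35, true HR 0.5, early/late start (all assumed, 600 replicates).**
- Early starters suppress faster (HR 2); 70% of resistant and 40% of other subjects start early. RNA only: HR 0.61, power 25%. With timing: 0.49, 44%.
- Early starters suppress more slowly (HR 0.5), same split. RNA only: 0.45, 53%. With timing: 0.52, 37%. The bias reverses.
- Timing unrelated to suppression: 0.47 vs 0.46, so no bias.

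**6. Effect modification.** If resistance acts only with early start (HR 0.4 early, 1.0 late), both models give HR 0.65, with power 24% (RNA only) and 20% (with timing). A main effect of timing does not recover this.

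**The case against.** The strongest reply is that timing is not ignored. Both 5.b and the opening of 5.c.2 plan ungated exploration of the interval and time to suppression. A reader might infer from the gate that a null result would end all work on timing; those two places do not support that. What stands is narrower. They treat timing as an exposure of interest, promise no timing-adjusted resistance effect, and conflict with the gate.

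A reader might also infer that a real resistance effect would be masked and reported as absent. The documents relate timing neither to resistance nor to suppression, so the bias could run either way or be nil. CD4 count and RNA at ARV start were similar between the pilot groups (p=.5 and p=.4), though timing by group is not given.

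It is tempting to read the pilot hazard ratio of 2.3 as a sign of confounding. It rests on ten subjects (CI 1.1-4.6) on at least three active agents, a group outside the planned contrast, and nothing links it to timing. A claim of inflated false positives is also fragile. With no true effect and unfavourable imbalance, simulated rejection rates were 12.2% vs 7.7% with timing included in one run (18 vs 35), and 5.0% vs 4.8% in another (11 vs 35, early/late start).

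Finally, different covariates for two outcomes are no contradiction in themselves, and a full covariate list may sit in a SAP that is not shown. That is fair, but this protocol does fix a covariate for the analysis and a significance condition for timing, and those are what need changing.

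**Conclusion.** The point holds as a matter of specification. The primary suppression comparison names RNA alone and gates timing on significance, its sibling model does not, and no section commits to a timing-adjusted resistance effect on suppression. The change is worth making because it is cheap and protects a non-randomised comparison in which ARV start varied widely (pilot median 45 days, IQR 24-107).

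The size is unknown. For balanced groups the power gain runs from about 2 points at a timing log-hazard of 0.25 per SD to about 10 points or more at 0.5 and above. It is less if RNA at ARV start already carries part of the timing effect. Which RNA value is meant is itself unclear: 5.a defines baseline as the first available specimen, whereas the pilot adjusted for RNA at treatment start. The resistance HR, the timing effects, the group imbalances and the use of 53 subjects are all assumptions, so these figures illustrate the risk and do not predict the result.

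**What to change.** In 5.c.2:
- Pre-specify the interval from estimated HIV-1 infection to ARV start (for example log days) as a covariate alongside HIV-1 RNA in the primary Cox model for time to suppression, fitted whatever the RNA-only result.
- Remove the significance condition for timing, so that this paragraph agrees with secondary objective 1 in 5.b and the opening of 5.c.2.
- Report the RNA-only model as a sensitivity analysis.
- Label a resistance-by-timing term as exploratory. It is the term that addresses the weakening effect raised in the Introduction, which a main effect does not test.

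Cost: a few sentences of analysis text and one degree of freedom in the primary model. Estimated infection date and ARV start date are already recorded, so no new data are needed. The downside is a slight loss of precision if timing proves unrelated to suppression.
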